## Background

Minimally invasive surgery, which includes both laparoscopic and robot-assisted surgery, has undoubtedly been one of the most significant advances in surgery during the past decade and is now the preferred approach for many surgical procedures [1–8]. Minimally invasive surgery aims to reduce postoperative pain and complications and shorten the time to functional recovery [1–8].

Minimally invasive distal pancreatectomy (MIDP) was first described in 1994 by Cuschieri et al. [9] Since then, several observational cohort studies from expert centers have suggested that MIDP is safe, feasible and cost-effective in the treatment of benign, premalignant and malignant lesions of the distal pancreas [10, 11]. These suggestions were confirmed by several systematic reviews of cohort studies that reported reductions in intraoperative blood loss, blood transfusion, complications, wound infections and shorter hospital stay, and an increased rate of spleen preservation, all in favor of the minimally invasive approach [10, 11].

Regarding oncologic parameters, including resection margins and lymph node retrieval, the minimally invasive approach is considered to be at least non-inferior to conventional open distal pancreatectomy (ODP) [12–15]. Case-matched studies, however, have not confirmed the presumed benefits of MIDP [10], indicating that confounding by indication has clearly played a role in the reported results in cohort studies. This is confirmed by a difference in baseline characteristics as reported in many series, such as smaller tumor size in the MIDP group [11]. It is therefore currently unknown whether MIDP, as a routine strategy, actually offers clinically relevant advantages over ODP. Most cohort series were performed in high-volume expert centers, so it is uncertain whether these outcomes of MIDP are generalizable [10]. Hence, randomized controlled trials are needed in order to provide high-quality evidence on the benefits of MIDP over ODP.

Minimally invasive approaches are often assumed to be more expensive than open surgery, because of the need for expensive surgical equipment and sometimes prolonged operative times. However, for several procedures, such as appendectomy, cholecystectomy and colectomy, no difference in overall costs has been demonstrated, mainly because reduced hospital stay balanced the higher procedural costs [16]. The current literature is unclear as to the cost difference between MIDP and ODP [10].

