### Statistical aspects

#### Sample size calculation

The LEOPARD trial is designed as a superiority trial, hypothesizing that the time to functional recovery is significantly shorter after MIDP compared with ODP. Based on the most recently published meta-analysis [11] and Dutch nationwide data, a time to functional recovery of 8 days in the control group (ODP) versus 6 days in the intervention group (MIDP) is expected with a standard deviation of 3 days. The significance level (α) is set at 0.05 and power (1-β) at 80%. The sample size needed in each arm, calculated using the independent samples *t* test, is 36 patients. Including 15% crossover from the MIDP to ODP and a rate of 2% loss to follow up (based on previous studies), a total of 51 patients will be randomized in each group, so a total of 102 patients will be randomized in the LEOPARD trial.

After completion of data collection in the first 75 patients, the data safety monitoring board will assess potential data skewness and homogeneity of variance for time to functional recovery. When a non-parametric test seems indicated for the comparison of MIDP versus ODP on time to functional recovery, the total sample size will become the calculated sample size (102) divided by the asymptomatic relative efficiency parameter of the Mann–Whitney *U* test (0.955). In that case, a total of 108 patients will be randomized in the LEOPARD trial. Procedures performed using the robot DaVinci® Surgical System are allowed in this trial, but will be analyzed separately during the cost analysis.

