#### Statistical analysis

Primary and secondary outcomes will be crosschecked with data from primary sources and a blinded adjudication committee will check them against the definitions, which were established before the start of this trial. Categorical variables will be compared using the chi-square or Fisher’s exact test as appropriate, and values will be expressed as proportions. The distribution of continuous variables will be determined using visual inspection and the Kolmogorov-Smirnov test.

For comparison of normally distributed continuous variables the independent samples *t* test will be used and values will be expressed as means with standard deviations. Continuous non-normally distributed variables will be compared using the Mann–Whitney *U* test and values will be expressed as medians with interquartile ranges. Measures of association will be expressed as relative risks with 95% confidence intervals. A difference with a two-tailed *P*-value <0.05 will be considered statistically significant.

Analyses will be performed based on intention-to-treat principles, meaning that converted MIDP will be assessed in the MIDP group. A multivariable linear regression model will be used to assess potential differences between groups in the primary outcome in the presence of potentially confounding factors. Linear mixed modeling will be applied to estimate differences between groups in successive EQ-5D-5 L and QLQ-C30 assessments over time. For exploratory purposes a secondary analysis will be performed comparing outcomes in patients with malignant versus non-malignant disease, comparing completed MIDP (i.e. no conversion) versus ODP and comparing time to functional recovery between MIDP and ODP in patients with complications (Clavien-Dindo score ≥ III) and without complications.

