There is no obvious clinical diversity in patients diagnosed with left-sided pancreatic disease, as these lesions are found in both women and men, at all ages, with different ethnicity. All of these demographic diversities, except for children, will be fully represented in the LEOPARD trial and the investigated procedures are uniform for all patients. The LEOPARD trial hypothesizes a superior value of MIDP for time to functional recovery and therefore all indications for elective distal pancreatectomy (with or without splenectomy) can be included. The Yonsei criteria will ensure oncological safety in patients diagnosed with pancreatic cancer within this trial, as it increases the probability of achieving R0 tumor resection margins [22]. Additional analyses will be performed to investigate the outcomes in several subgroups of patients (e.g. those with non-malignant versus malignant disease and those with and without complications).

Within the LEOPARD trial, laparoscopic surgery and robot-assisted surgery are both considered minimally invasive and therefore both are allowed in the “minimally invasive” arm. Furthermore, no clear differences in hospital stay and morbidity have been shown for one versus the other [10].

Patient blinding should be performed (if possible) in randomized controlled trials to decrease the influence of several types of bias and should especially be considered in trials with patient-reported outcome measures as the primary and/or secondary outcome [42]. Functional recovery is partly patient-reported (e.g. pain perception) and is easily influenced by the patient’s expectation. Patient blinding is therefore essential to eliminate the Hawthorne effect, which means that if patients know that they have been allocated to a specific arm, their behavior and response will consequently be influenced [43]. Patient blinding in randomized controlled trials in abdominal surgery has been successfully performed in previous trials [8, 31], but its impact remains to be assessed [44].

In conclusion, the LEOPARD trial is a multicenter randomized controlled trial investigating time to functional recovery after MIDP versus ODP. This trial aims to provide level-1 evidence on the added value of the minimally invasive approach. When this hypothesis is confirmed, it will enhance the worldwide implementation of MIDP and consequently improve patient outcomes.

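### The cost analysis sets robot cases apart without saying that they stay in the MIDP arm, and the only stated rule for skewed costs does not estimate the mean cost difference

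*Protocol article*

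**What the plan says.** **Robot cases.** The last sentence of Sample size calculation says that procedures with the robot system "are allowed in this trial, but will be analyzed separately during the cost analysis". The Discussion says that "laparoscopic surgery and robot-assisted surgery are both considered minimally invasive and therefore both are allowed in the" minimally invasive arm, and the section on conversion defines MIDP as laparoscopic or robot-assisted. Randomization is between MIDP and ODP, stratified by center and by malignant versus non-malignant indication. Robot use is neither randomized nor a stratification factor. Statistical analysis commits the trial to intention-to-treat, but the only consequence it spells out is that converted patients are assessed in the MIDP group.

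**Skewed costs.** Intra-operative and postoperative costs are listed under Secondary outcomes, and costs are part of the aim stated in the Background. For continuous variables that are not normally distributed, Statistical analysis prescribes the Mann-Whitney test, and "values will be expressed as medians with interquartile ranges". It adds separate models for the primary outcome (linear regression) and for quality of life (mixed model). It adds none for costs and does not exempt them from the general rule.

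**The concern.** These are two separate problems, and each has its own consequence.

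The first concerns who is compared. Robot-assisted surgery can occur only in the MIDP arm. If the main cost comparison leaves those patients out, the remaining MIDP patients are a subset not formed by randomization, while the ODP arm stays whole. The MIDP figure would also lose any extra cost of the robot, although the robot belongs to the strategy being tested.

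The second concerns what is estimated. Total cost equals the number of patients times the arithmetic mean, so the mean difference shows whether one strategy costs more than the other overall. Medians and ranks give little weight to how expensive the few costly stays are. If one arm has a dearer procedure and the other has more costly stays, the median and the mean can favor different arms.

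What is at stake is the trial's statement on costs, which is a named aim but a secondary outcome.

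**Working it through.** **The plan's own figures.** The article gives no figure for the cost analysis. Its only calculation is for the primary outcome. It assumes 8 days after ODP against 6 days after MIDP, an SD of 3 days, α = 0.05 two-sided, and power 80%.
- Per arm: 2 × (1.96 + 0.84)² × 3² / 2² = 35.3, so 36.
- With 15% crossover as dilution and 2% loss: 36 / 0.85² / 0.98 = 50.8, so 51 per arm and 102 in total.
- With the Mann-Whitney efficiency: 51 / 0.955 = 53.4, so 54 per arm and 108 in total.

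All three agree with the article. They matter here only because they give 51 patients per arm for the illustrations.

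**Inputs the documents do not give.** Cost means, spread and skewness, the share of robot cases and their extra cost are all assumed below, in thousands (k) of an arbitrary currency. The one figure from the article is the 17% major complication rate after MIDP training (Background).

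**Point 1: leaving robot cases out.** Let p be the robot share, R the robot mean and L the laparoscopic mean. The whole-arm mean is (1 − p)L + pR = L + p(R − L). Leaving robot cases out therefore lowers the MIDP mean by p(R − L).

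| Robot share | Shift at 1k extra | Shift at 2k | Shift at 3k | MIDP patients left of 51 |
|---|---|---|---|---|
| 5% | 0.05k | 0.10k | 0.15k | about 48 |
| 10% | 0.1k | 0.2k | 0.3k | about 46 |
| 20% | 0.2k | 0.4k | 0.6k | about 41 |
| 30% | 0.3k | 0.6k | 0.9k | about 36 |
| 40% | 0.4k | 0.8k | 1.2k | about 31 |

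**Point 2: median against mean, first model.** ODP costs 10k (SD 2k) and MIDP 11k (SD 2k). Each major complication adds 20k, at a rate of 17% after MIDP and an assumed rate after ODP.
- Mean: base + 20 × rate. MIDP: 11 + 20 × 0.17 = 14.4k.
- Median: the value m at which (1 − rate) × Φ((m − base)/2) = 0.5, since complicated stays lie far above it. MIDP: Φ = 0.5/0.83 = 0.602, so m = 11 + 2 × 0.26 = 11.5k.

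| Assumed ODP rate | ODP mean | ODP median | MIDP − ODP, means | MIDP − ODP, medians | Signs |
|---|---|---|---|---|---|
| 17% | 13.4k | 10.5k | +1.0k | +1.0k | agree |
| 20% | 14.0k | 10.6k | +0.4k | +0.9k | agree |
| 25% | 15.0k | 10.9k | −0.6k | +0.7k | opposite |
| 30% | 16.0k | 11.1k | −1.6k | +0.4k | opposite |

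At 25%, the probability that a random MIDP patient costs more than a random ODP patient has three parts. With no complication in either, or in both, it is Φ(1/(2√2)) = 0.638; with a complication after MIDP only, it is practically 1. So 0.83 × 0.75 × 0.638 + 0.17 × 0.75 + 0.17 × 0.25 × 0.638 = 0.55.

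**Point 2, second model.** Lognormal costs have mean = median × exp(s²/2), where s is the SD on the log scale. Take medians of 9k (MIDP) and 10k (ODP), with s = 0.5 in ODP. The ODP mean is 10 × exp(0.125) = 11.33k.
- MIDP s = 0.5: 9 × exp(0.125) = 10.20k, difference −1.13k. The signs agree.
- MIDP s = 0.8: 9 × exp(0.32) = 12.39k, difference +1.06k. The signs oppose.
- The mean difference is zero where s²/2 = 0.125 + ln(10/9) = 0.230, that is at s = 0.68.

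In 5,000 simulated trials of 51 per arm with MIDP s = 0.8, the sample median and mean differences had opposite signs in about 47%. The Mann-Whitney test significantly favored MIDP in about 12%, although MIDP was dearer by the mean. With s = 0.5 in both arms, opposite signs still arose by chance in about 15%.

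**The case against.** The strongest reply is that separate analysis need not mean exclusion. A breakdown by technique, reported beside a comparison of the whole arms, fits both the intention-to-treat commitment and the definition of MIDP. This stands. A reader might infer that robot cases are removed and that randomization is therefore broken, but the text does not say so. It leaves two sentences unreconciled, and that is the point made here. Nor does the article say when, or by whom, robot use is decided. It shows only that robot use is not randomized.

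A second reply is that the Mann-Whitney paragraph is a general rule, and that the cost analysis, which the article mentions as something of its own, may be set out in a full protocol or analysis plan that is not shown. This stands in part: one cannot conclude that costs will be analyzed by that rule alone. But the rule is stated, it covers skewed costs as worded, and nothing exempts them.

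A third reply concerns the Background remark that costs came out equal "mainly because reduced hospital stay balanced the higher procedural costs". It describes appendectomy, cholecystectomy and colectomy. A reader might take it as this trial's own cost question, but the article does not adopt it as such. The case for means rests on the link between mean and total, not on that remark.

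Finally, the illustrations are assumed and imprecise. In the first model at 25%, the cost SDs are √(4 + 400 × 0.25 × 0.75) = 8.9k and √(4 + 400 × 0.17 × 0.83) = 7.8k. The standard error of the mean difference with 51 per arm is √((79.0 + 60.4)/51) = 1.65k, so the 95% interval is about ±3.2k around −0.6k. A mean comparison would itself put MIDP as dearer in about Φ(−0.6/1.65) = 36% of trials. The 0.55 above is less than one null standard error, √(103/(12 × 51 × 51)) = 0.057, from 0.50, so the rank test would seldom be significant. All of this stands. It limits how much any cost analysis of this size can show, but it does not make the median or the rank test an estimate of the mean difference.

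**Conclusion.** Both points hold, separately, and for a secondary outcome only.

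1. The article does not settle whether robot cases stay in the main cost comparison. If they are left out, the comparison is no longer the randomized one, and the MIDP mean moves by robot share times extra robot cost: 0.05k to 1.2k over the assumed ranges. If separate analysis means an added breakdown, no harm is done, and only the wording needs repair.
2. As written, skewed costs are compared by ranks and summarized by medians, which does not estimate the difference in mean or total cost. The sign can differ under some cost distributions. In the models above this needs a trade-off between a dearer procedure and enough fewer costly stays, or a clearly wider cost spread in one arm. With equal complication rates or equal log-scale spread the signs agree.

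A reader might infer that the reported cost result will point the wrong way. The documents do not support that, because they contain no cost data from which to judge how likely it is. The two points also have different consequences: the robot sentence does not cause a sign reversal, and the median rule does not disturb randomization. The primary outcome and the sample size are untouched.

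**What to change.** State in the analysis plan, before the final analysis, that:
- the main cost analysis compares arithmetic mean cost per randomized patient by allocated arm, with all robot-assisted cases kept in MIDP and a bootstrap 95% confidence interval for the mean difference;
- costs are exempt from the Mann-Whitney and median rule (medians and interquartile ranges may still be shown as description);
- the laparoscopic and robot breakdown is a labelled sensitivity analysis, with a note that it is not a randomized comparison.

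The robot sentence in Sample size calculation should be reworded to match.

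The cost is a few sentences and slightly more analysis work, with no new data or patients. The MIDP cost figure may become less favourable once robot cases are kept in, and the interval for the mean difference may be wide.

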#### Statistical analysis

Primary and secondary outcomes will be crosschecked with data from primary sources and a blinded adjudication committee will check them against the definitions, which were established before the start of this trial. Categorical variables will be compared using the chi-square or Fisher’s exact test as appropriate, and values will be expressed as proportions. The distribution of continuous variables will be determined using visual inspection and the Kolmogorov-Smirnov test.

For comparison of normally distributed continuous variables the independent samples *t* test will be used and values will be expressed as means with standard deviations. Continuous non-normally distributed variables will be compared using the Mann–Whitney *U* test and values will be expressed as medians with interquartile ranges. Measures of association will be expressed as relative risks with 95% confidence intervals. A difference with a two-tailed *P*-value <0.05 will be considered statistically significant.

Analyses will be performed based on intention-to-treat principles, meaning that converted MIDP will be assessed in the MIDP group. A multivariable linear regression model will be used to assess potential differences between groups in the primary outcome in the presence of potentially confounding factors. Linear mixed modeling will be applied to estimate differences between groups in successive EQ-5D-5 L and QLQ-C30 assessments over time. For exploratory purposes a secondary analysis will be performed comparing outcomes in patients with malignant versus non-malignant disease, comparing completed MIDP (i.e. no conversion) versus ODP and comparing time to functional recovery between MIDP and ODP in patients with complications (Clavien-Dindo score ≥ III) and without complications.

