### Trial population

All adult patients with an indication for elective distal pancreatectomy (with or without splenectomy) because of suspected or proven symptomatic benign, premalignant or malignant disease of the distal pancreas, from 17 centers performing pancreatic surgery in The Netherlands will be assessed for eligibility.

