### Randomization

Patients will be randomized centrally by the trial coordinators using an online randomization module (ALEA, Clinical Research Unit, Academic Medical Center, Amsterdam, The Netherlands) in a 1:1 ratio between MIDP and ODP, as shown in Fig. 1. Randomization will be stratified by center to balance differences in the surgical procedure and general treatment regimens and by the indication for surgery (malignant versus non-malignant disease). Permuted-block randomization will be used to provide treatment allocation in equal proportions, with block sizes that will be subject to random variation. This will be concealed to all investigators involved in the trial.

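### Randomization is stratified by center and indication, but the stated primary comparison ignores both, which gives up precision to the extent that they predict recovery

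*Protocol article*

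**What the plan says.** Protocol article, Randomization: "Randomization will be stratified by center to balance differences in the surgical procedure and general treatment regimens and by the indication for surgery" (malignant or non-malignant). Allocation is "in a 1:1 ratio between MIDP and ODP", and "Permuted-block randomization will be used to provide treatment allocation in equal proportions, with block sizes that will be subject to random variation". Under Trial population, patients come "from 17 centers performing pancreatic surgery in The Netherlands will be assessed for eligibility".

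Sample size calculation: the trial is sized with the independent samples t test. The Mann–Whitney U test is foreseen as the replacement for comparing the arms on time to functional recovery if the data look unsuitable for a parametric test.

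Statistical analysis: continuous variables go to one of these two tests according to their distribution. Neither uses the strata. The same section adds: "A multivariable linear regression model will be used to assess potential differences between groups in the primary outcome", allowing for possible confounders. It does not name those factors, does not mention center or indication among them, and does not rank this model against the unadjusted test. In that section indication appears only in an exploratory comparison of malignant with non-malignant disease.

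**The concern.** Stratifying on a factor is worthwhile because the factor is thought to bear on outcome, and the protocol gives differences in procedure and care regimen as its reason for using center. Stratified allocation balances the arms on these factors, so the difference in means varies less from trial to trial than under simple randomization. An unadjusted t test takes no credit for this. It leaves the between-stratum variance in its error term, so the standard error is overstated, the test is conservative and the t-test interval is wider than it need be.

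At stake is efficiency in a trial of 102 patients planned at 80% power. It is also left open which result leads if the adjusted and unadjusted analyses disagree.

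**Working it through.** **Inputs from the protocol (Sample size calculation).** "a time to functional recovery of 8 days in the control group (ODP) versus 6 days in the intervention group (MIDP) is expected", so the difference is 2 days; SD 3 days; two-sided α 0.05; power 80%; 15% crossover; 2% loss to follow-up; 51 per arm.

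**Input not in the protocol.** R², the share of outcome variance explained by center and indication together. It is assumed here to lie between 0 and 0.30, split equally between the two factors in the simulations.

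**1. The plan's own figure.** n = 2(1.960 + 0.842)² × (3/2)² = 35.3, so 36 per arm (exact t test: 36.3). Inflation: 36 / (0.85² × 0.98) = 36 / 0.708 = 50.8, so 51 per arm and 102 in total. This matches. With the diluted effect 2 × 0.85 = 1.7 days and 51 × 0.98 ≈ 50 evaluable per arm, t-test power is 0.801.

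**2. Strata.** 17 × 2 = 34 possible strata, and 102 / 34 = 3 patients per stratum on average.

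**3. Effect of adjustment, by formula.** Assume exact balance within strata, total SD 3 and 50 per arm.

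- SE used by the t test: 3 × √(2/50) = 0.60.
- True SE: 0.60 × √(1 − R²).
- Power of the t test: 1 − Φ[(1.96 × 0.60 − 1.7) / true SE].
- Power of the adjusted test: 1 − Φ[1.96 − 1.7 / true SE].

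At R² 0.20 the true SE is 0.60 × √0.80 = 0.537. For the t test, (1.176 − 1.7) / 0.537 = −0.976, giving power 0.836. For the adjusted test, 1.96 − 1.7 / 0.537 = −1.208, giving 0.886.

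**4. Simulation of the proposed model** (indication fixed, center random intercept). Set A: N = 102, 17 centers of unequal size, blocks of 2, 4 or 6 within center by indication, effect 1.7 days, 4000 trials per setting. The block sizes are assumed, since the protocol gives none. Set B is a separate set of simulated trials with the same model.

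| R² | Formula: t test / adjusted | Gain (points) | Set A: t test / mixed model | Set B: t test / mixed model |
|---|---|---|---|---|
| 0 | 0.809 / 0.809 | 0 | 0.80 / 0.81 | 0.80 / 0.81 |
| 0.10 | 0.821 / 0.848 | 2.6 | 0.81 / 0.84 | 0.82 / 0.85 |
| 0.20 | 0.836 / 0.886 | 5.1 | 0.83 / 0.88 | 0.82 / 0.88 |
| 0.30 | 0.852 / 0.923 | 7.1 | 0.84 / 0.92 | 0.85 / 0.92 |

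The normal formula gives 0.809 at R² 0 where the exact t calculation gives 0.801.

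**5. Type I error.** For the t test the exact-balance formula is 2[1 − Φ(1.96 / √(1 − R²))] = 0.039, 0.028 and 0.019 at R² 0.10, 0.20 and 0.30. Simulated values are less extreme, because balance within small strata is imperfect: 0.033–0.037 at R² 0.20–0.30 across sets A and B. In set A the mixed model lay between 0.049 and 0.057. At R² 0 the t test itself showed 0.059. It holds its level there, so that excess is simulation error.

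**6. The alternative with 17 fixed center effects** (3000 simulated trials per setting). Power, t test against model: 0.81 / 0.77 at R² 0; 0.81 / 0.81 at 0.10; 0.83 / 0.87 at 0.20; 0.84 / 0.91 at 0.30. Mean 95% interval width in days: 2.35 against 2.19 at R² 0.20 (ratio 1.07) and 2.34 against 2.04 at 0.30 (ratio 1.15). In this set t-test type I error was 0.033 and 0.027 at R² 0.20 and 0.30.

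**7. Rank-based route.** In the same set the unadjusted Mann–Whitney test had power 0.79, 0.78, 0.82 and 0.82 at R² 0, 0.10, 0.20 and 0.30 (normal outcomes, N = 102), and type I error 0.031 and 0.028 at R² 0.20 and 0.30. A stratified rank-based alternative was not computed.

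**The case against.** The strongest reply is that nothing here is invalid. The trial was sized for the unadjusted t test, the size reproduces, and simulated t-test power is 0.80–0.85 at every assumed R². Any departure in type I error is downward. All of that stands.

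Second, an adjusted analysis of the primary outcome is already planned, and a condensed article may leave its covariates to the full protocol or SAP. This also stands, so the unnamed covariates are not held against the plan. A reader might infer that the regression leaves out the stratification factors, or that its covariates will be picked once the data are seen; the article says neither. What it does state is the unadjusted comparison, to which the sample size and its possible increase to 108 are both tied. That is a choice, not missing detail.

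Third, the gain depends on an R² that the protocol does not give, and adjustment can cost power. The first half stands. The second holds for 17 fixed center effects (0.77 against 0.81 at R² 0), but no loss appeared with a random intercept.

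It is also tempting to say that most blocks will stay incomplete. With block sizes not given, and 3 per stratum only an average over possible strata, that cannot be established.

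**Conclusion.** The point holds as one of efficiency and clarity. The stated primary comparison does not use the factors on which patients are randomized, and the one adjusted model is neither designated primary nor tied to them. The forgone power is roughly 0 points at R² 0, 2–3 at 0.10, 5–6 at 0.20 and 7–8 at 0.30, and the t test runs at about 3–4% instead of 5% at R² 0.20–0.30. These sizes rest on the assumed R², normal outcomes, SD 3, the diluted effect of 1.7 days and assumed small blocks.

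Three stronger readings are not supported:

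- A reader might infer that the trial is underpowered or open to false-positive results. It is neither: the planned power is kept and the test errs on the conservative side.
- Comparing adjusted power with a fixed 80% would overstate the gain (8 points instead of 5–6 at R² 0.20), because the t test's own power also rises above 80% when the strata are prognostic.
- Intervals that are too wide concern the t-test route only. The Mann–Whitney route reports medians with interquartile ranges and names no interval for the treatment difference.

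**What to change.** State that the primary comparison of time to functional recovery is a model with arm, indication as a fixed effect and center as a random intercept, and not 17 fixed center effects. Specify small-sample degrees of freedom, since the model's simulated type I error reached 0.057. If the analysis is rank-based, either stratify it by indication with small centers pooled by a rule set in advance, or use a proportional-odds model with the same terms. Keep the unadjusted test as supportive, and say that the adjusted result leads if the two differ.

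The cost is wording, slightly more analysis work and reliance on a mixed model with small centers. Both factors are known at randomization, so no new data are needed, and the sample size can stay as it is. Under Trial status, 78 of 102 patients had been randomized at submission, so the change could be made and dated before any comparative results are seen.
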